### Safety review and monitoring

The trial will be conducted in two phases. The initial pilot phase (cohort 1) includes 10 adults (≥ 16 years old) who will be recruited and monitored closely sequentially during the study course. Each patient will be administered either anakinra or placebo for 4 days (5 anakinra, 5 placebo).

A Data Monitoring Committee (DMC) review will take place when day 5 data are available from the first 10 patients enrolled. Based on a review of all reported serious adverse events and overall clinical outcomes, the DMC will recommend continuation, amendment of the protocol or stopping the study. Following satisfactory safety review after the 10
^th^ patient, the study will advance to the next phase to enrol the remaining 150 patients. The DMC will continue performing interim reviews after every 50 recruited patients to evaluate safety and tolerability of the study drug. In the event that any unusual or unpredictable serious adverse event occurs, the study team will temporarily pause recruitment and report data to local ethics committees for review.

The study drug will be stopped for an individual if they (1) request drug discontinuation ; (2) develop any AEs which require discontinuation of the study medication, including severe hypersensitivity reaction, severe acute renal impairment (eGFR below 30mL/min/1.73m
^2^), severe neutropenia (absolute neutrophil count < 0.5 × 10
^9^/L for at least 2 consecutive days [24 ± 6 hours]).

All AEs occurring during the trial will be recorded in the CRF regardless of their relativity with trial medication and will be reported to OxTREC in the annual review form, to the DMC in accordance with the DMC charter and to local ECs following local regulations. Clinical and Laboratory events will be graded according to Common Terminology Criteria for Adverse Events (CTCAE) definitions.

In cases of adverse events leading to i) early stopping of the study drug; or ii) patients having to stay in hospital for longer than 5 days, the treatment for these cases will be at discrete of the attending physicians. If study drug discontinued early due to adverse events, participants will be followed up until the events have resolved for stabilized. Patients who wish to continue to stay in the trial will be followed-up as per protocol. The blood samples and data required in the study will continue to be collected until study day 5. The summary of clinical outcome will be collected at discharge. All patients will be invited to come back for the final follow-up visit at around day 30 of illness and at 3 months.

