### Secondary endpoints

The secondary endpoints are: 30-day mortality; change in mSOFA score at day 7 post randomization; number of days in ICU; number of days in hospital; number of individuals with serious adverse events (time-period 1–5 days and 6–30 days); number of adverse events per individual during the whole study course; change in ALT and platelets over 5 days following randomization; change in ferritin and CRP levels over 5 days following randomization and until day 30 after illness onset; time to normalization of platelets (defined as >150 ×10
^9^/l) and neutrophils (>2 ×10
^9^/l); platelet nadir; fever clearance time (defined as <37.5 °C for at least 48 hours; measured 4 times/day); duration of viraemia (number of days to first negative qPCR and NS1); AUC viraemia (from enrolment to negative); EQ-5D-5L questionnaire score at hospital discharge and day 30.

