### Data collection

Study data will be collected using an electronic CRF, except identification information which will only be recorded on paper CRF. All patients will be reviewed daily until discharge. Standardized clinical information and a full blood count, biochemistry and research blood sampling will be performed at each visit, plus any other tests deemed necessary by the attending physician. Details of all adverse events will be recorded on specific forms. An ultrasound scan of the chest and abdomen to assess vascular leakage will also be performed on alternate days in all participants by a study staff member using the portable ultrasound scan machine provided by OUCRU.

During the follow-up visits at day 30 and 3-months after the fever onset, patients will be asked about any newly emerging or persisting symptoms using a standardized questionnaire. Research blood samples will be taken for convalescent serology, immunology studies, full blood count and biochemistry tests.

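### Two sections give different end points for daily study data in patients kept in hospital after day 5 by an adverse event, which leaves several secondary endpoints open to informative censoring

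*Protocol article*

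**What the plan says.** The last paragraph of Safety review and monitoring in the protocol article opens with the patients it concerns: "In cases of adverse events leading to i) early stopping of the study drug; or ii) patients having to stay in hospital for longer than" (the threshold for a prolonged stay is 5 days). For these patients it then says several things:

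- After an early stop for an adverse event, "participants will be followed up until the events have resolved for stabilized".
- Those who choose to remain in the study have the usual protocol follow-up.
- On the duration of sampling, it states: "The blood samples and data required in the study will continue to be collected until study day 5".
- An outcome summary is taken when the patient is discharged, and everyone is invited back at about day 30 of illness and at 3 months.

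The next section, Data collection, says "All patients will be reviewed daily until discharge". On the content of these reviews, it adds: "Standardized clinical information and a full blood count, biochemistry and research blood sampling will be performed at each visit". It names no exception for patients with adverse events.

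Secondary endpoints lists several outcomes that can need observation after day 5: change in mSOFA at day 7, time to normalization of platelets and neutrophils, fever clearance over 48 hours with four readings a day, days to first negative qPCR and NS1, and viraemia AUC up to negativity. Statistical considerations assigns the two normalization times to a Cox model.

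**The concern.** For a patient in hospital on day 6 or later because of an adverse event, one section ends study samples and data at day 5 and the other continues them daily to discharge. The sentence on follow-up as per protocol does not settle the matter, because the protocol contains both rules.

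If the day-5 rule is applied, the shorter observation falls on patients picked out by something that happened after randomisation and may be related to treatment. A Cox model assumes that a patient censored at day 5 has the same prospects as those still under observation. A patient kept in hospital by an adverse event probably recovers more slowly, so the censoring would be informative. Severe neutropenia is among the events that fall under "develop any AEs which require discontinuation of the study medication", and neutrophil recovery is itself an endpoint. If such events differ in number between the arms, the distortion differs too.

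**Working it through.** The plan has no figure of its own on this point. The check sets the data windows beside the endpoint windows and then asks how large the effect could be.

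**Step 1. Which endpoints fit inside day 5?** Windows are from Primary endpoint, Secondary endpoints and Statistical considerations.

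| Endpoint | Data needed | If daily data end at day 5 |
|---|---|---|
| Delta mSOFA (primary) | 4 days | unaffected |
| ALT, platelet, ferritin and CRP slopes | 5 days | unaffected |
| 30-day mortality; day-30 ferritin and CRP; EQ-5D-5L | discharge or day 30 | unaffected |
| Days in ICU and in hospital | dates | should be recoverable from the discharge summary |
| Change in mSOFA at day 7 | day 7 | missing, since 7 > 5 |
| Platelet and neutrophil normalization | serial counts, no fixed end | censored at day 5 if not yet reached |
| Fever clearance | 48 h of readings below 37.5 °C | clearance after day 3 cannot be confirmed (5 − 2 = 3) |
| Viraemia duration and AUC | serial qPCR/NS1 to negativity | incomplete if still positive at day 5 |
| Platelet nadir | serial counts | missed if it falls late |

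**Step 2. Does other follow-up fill the gap?** Event follow-up to resolution or stabilisation is written only for patients whose drug was stopped early. Patients in the second group, those with a prolonged stay, do not have it. No sampling frequency is given for it, and a neutropenia can count as resolved or stabilised below the endpoint threshold of >2.0 ×10⁹/l. A discharge summary does not supply serial counts, temperatures or qPCR. The day-30 blood count shows only that recovery occurred by then.

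**Step 3. How many patients?** The documents give no rate for these adverse events. Assuming 5%, 10% or 20% of 160 patients:

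- 0.05 × 160 = 8
- 0.10 × 160 = 16
- 0.20 × 160 = 32

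**Step 4. How large could the bias be?** This is an illustration only, since every input except 80 per arm is assumed. Affected patients recover between days 7 and 11. All others have gamma-distributed recovery times with mean 5 days. The model is Cox with Efron ties. The hazard ratio (HR) for recovery, anakinra versus placebo, is computed once with full follow-up and once with affected patients censored at day 5. The share of the delay that is hidden is 1 − ln(HR censored)/ln(HR full). With 12 affected on anakinra and 3 on placebo:

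| Gamma shape | HR, full | HR, censored | Share hidden |
|---|---|---|---|
| 2 (widely spread) | 0.91 | 0.90 | none |
| 4 | 0.86 | 0.90 | 1 − 0.105/0.151 = 30% |
| 10 (tightly clustered) | 0.79 | 0.91 | 1 − 0.094/0.236 = 60% |

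With 8 versus 2 affected and shape 8, the HR moved from 0.84 to 0.94, a share of 1 − 0.062/0.174, about 65%. With 4 versus 4 it stayed close to 1 either way. The result therefore depends on the imbalance between arms and on how tightly the other patients' recovery times cluster, and the documents fix neither.

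**The case against.** The strongest reply is that the day-5 sentence is a floor. It follows the statement that patients who stay in the trial are followed as per protocol, it does not say that collection is limited to day 5, and day 5 is the trial's core sampling window. On that reading it only ensures that sampling does not stop when the drug stops. This is plausible for early stoppers. It fits poorly with the other group, patients whose stay exceeds 5 days: for them a day-5 end says nothing useful as a minimum, and the next sentence offers only a summary at discharge.

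A second reply is that this is a condensed article. It cites section numbers that it does not contain, and the full protocol may hold a clear sampling schedule. That may be so, but the article itself states two incompatible end points, which is different from leaving a detail out.

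A reader might also infer more than the text supports:

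- **A deliberate two-tier schedule**, with toxicity patients followed to day 5 and everyone else to discharge. Data collection covers all patients, so the fault is an unreconciled contradiction.
- **That all study data end at day 5.** Event follow-up after an early stop, the discharge summary and the day-30 and 3-month visits remain.
- **That a patient who stops for neutropenia and recovers on day 9 would never be recorded.** Event follow-up may well capture that recovery, though perhaps not the date on which the count passes 2.0 ×10⁹/l.
- **That about half of any delay would be hidden.** That figure needs assumed event counts, a large imbalance and tightly clustered recovery times. Adverse events that prolong stay could also be commoner on placebo if the drug works, which would reverse the imbalance.
- **That the gaps are confined to patients with toxicity.** Patients discharged early lose daily data too.

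**Conclusion.** The contradiction is real and should be removed. It concerns patients still in hospital after day 5 because of an adverse event, and it bears on a handful of secondary endpoints. Day-7 mSOFA is the clearest case, because its time point lies outside the day-5 window. The trial's primary conclusion is not at risk.

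Whether any bias arises depends on which sentence the site follows, how many patients have such events, and whether the arms differ. The documents settle none of these, so the size is unknown and may be negligible. It still merits correction because recruitment has been under way since January 2024, and serial measurements that were not taken cannot be recovered in the analysis.

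**What to change.** In Safety review and monitoring, replace the day-5 end point with a statement that study assessments and samples continue daily until discharge, as for all participants, whether or not study drug was stopped. Apply one censoring rule to everyone in the time-to-event analyses. For patients already recruited, establish which rule the site has been following.

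The cost is one sentence and a few more data days in the patients concerned. Data collection already provides for the sampling, and no treatment rule changes.

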### Data collection

Study data will be collected using an electronic CRF, except identification information which will only be recorded on paper CRF. All patients will be reviewed daily until discharge. Standardized clinical information and a full blood count, biochemistry and research blood sampling will be performed at each visit, plus any other tests deemed necessary by the attending physician. Details of all adverse events will be recorded on specific forms. An ultrasound scan of the chest and abdomen to assess vascular leakage will also be performed on alternate days in all participants by a study staff member using the portable ultrasound scan machine provided by OUCRU.

During the follow-up visits at day 30 and 3-months after the fever onset, patients will be asked about any newly emerging or persisting symptoms using a standardized questionnaire. Research blood samples will be taken for convalescent serology, immunology studies, full blood count and biochemistry tests.

### Statistical considerations

**
*Sample size.*
** Given that delta mSOFA score has an approximately normal distribution
^
25
^ with a standard deviation of 2.4, which was based on a cohort of 38 adults admitted with severe dengue, we would need a sample size of 80 patients per group to detect a between-group difference of at least 1.0 point with 80% power and 5% type-I error rate.

**
*Statistical analysis.*
** The primary endpoint (delta mSOFA score) and the secondary endpoints (ALT, CRP, PLTs and ferritin) will be analyzed using a linear mixed-effects model, which models their values over the first 4 days for mSOFA and 5 days for lab tests (as specified in sections 2.4.1 and 2.4.2). We will use a linear trend for time as fixed and random effects. The slope of this model reflects the change in value over time. Therefore, the effect of anakinra is measured as the difference in slope between treatment groups. This difference will be assessed via the interaction between time and treatment group in that model, and presented with a corresponding 95% confidence interval. For the change at day 30 (ferritin and CRP) we will use the difference with the value at randomisation. Mortality will be assessed by comparing Kaplan-Meier curves via log-rank test. The number of serious adverse events will be compared via 2×2 tables with chi-square tests, or Fisher’s exact test in case the expected number under the null hypothesis is smaller than 1 in at least one of the cells. Number of AEs per individual will be compared using Poisson regression, or quasi-Poisson regression in case of overdispersion. EQ visual analogue score will be compared via linear regression in case it has a fairly symmetric distribution; otherwise we will use beta-regression. Normalization of neutrophils will be defined as first time to reach normal range of >2.0 ×10
^9^/l and for platelets the first time to reach >150 ×10
^9^/l and will be assessed by Cox model. For viraemia AUC and duration outcomes we will also perform the analysis with correction for day of illness (DOI). The time of fever clearance is defined by the first time after which all readings are <37.5°C in the following 48 hours.

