## Background

Dengue continues to be a major public health burden in Vietnam and globally
^
1
^. While most clinical cases of dengue resolve after 1 week, approximately 5–10% of hospitalized patients will develop severe manifestations, usually during the critical phase (day 4–6 of illness)
^
2
^, allowing a window of opportunity to identify patients at risk of progression and intervene with a disease modifying agent
^
3,
4
^. However, thus far, no antiviral agents or adjunctive therapies have been found to alter disease outcomes in dengue
^
3–
6
^. Novel host directed therapeutics are urgently needed for patients with dengue, particularly those at high risk of developing severe disease.

Understanding of the mechanism underlying progression to severe disease has improved; it has been demonstrated that hypercytokinemia and an excessive host inflammatory response to infection are associated with life-threatening complications
^
2,
3
^. The dengue virus (DENV) replicates within monocytes and macrophages, and failure to clear these virus-infected cells by dysfunctional cytotoxic NK/CD8+ T cells can facilitate a hyperinflammatory state or “cytokine storm”, through persistent macrophage activation and ultimately end-organ damage. Therapeutic trials with broad immunosuppression using corticosteroids in dengue have so far been unsuccessful
^
5
^, likely due to unselected patient populations with insufficient stratification. Interleukin-1 (IL-1) is a key pro-inflammatory cytokine involved in the cytokine storm and also in dengue pathogenesis
^
7–
9
^. One of the safest and possibly most targeted ways of controlling this excessive inflammation is through IL-1 receptor (IL-1R) blockade
^
6
^.

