### Cytokine storm and inflammatory biomarkers

Previous studies have shown that features of Macrophage activation syndrome (MAS)/secondary HLH/hyperinflammation are more prevalent in severe dengue. Higher inflammatory biomarkers, including higher ferritin
^
8,
9,
15
^ and an early higher peak plasma IL-1R antagonist (IL-1RA) levels (a surrogate for IL-1 activity)
^
7
^, are associated with more severe clinical outcomes in dengue. In a cohort of 207 hospitalized dengue patients (children and adults) in Vietnam, 63% with severe disease and 33% with moderate disease had ferritin levels > 2000 ng/ml ([name], unpublished data). In another cohort of 135 adults with dengue shock in Ho Chi Minh City, median plasma ferritin measured within 24 hours of shock onset was 7671 ng/ml, but among those who did not survive their illness, median plasma ferritin was 71,573 ng/ml at enrolment, and 100,000 ng/ml 48 hours later
^
16
^.

While measurement of IL-1 activity is complicated due to low concentrations, local production and short half-life
^
7
^, ferritin testing is readily available in clinical practice. In this trial, we propose using ferritin as a screening biomarker to identify patients at high risk of severe and life-threatening dengue, in whom immunomodulation may improve clinical outcomes.

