## Methods

### Design

This is a double-blinded randomized placebo-controlled phase II trial of anakinra in patients diagnosed as having dengue with warning signs/severe dengue and hyperferritinaemia (>2000 ng/ml) (
Figure 1). The study will enrol 160 adults and children ≥ 12 years old admitted to the Hospital for Tropical Diseases, Ho Chi Minh City. Participants will be randomized 1:1 (anakinra:placebo) on electronic database system (Ennov) and stratified according to the ward of recruitment (Intensive Care Units/Emergency Department or the general dengue wards). Patients with warning signs or severe dengue (defined by 2009 WHO classification) and ferritin > 2000 ng/ml will be eligible for enrolment.

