### Inclusion and exclusion criteria

Patients will be eligible for study enrolment if they: (i) are more than or equal to 12 years of age; (ii) have a clinical diagnosis of dengue and at least one warning sign or severe dengue (based on the World Health Organization (WHO) 2009 or Vietnamese Ministry Of Health (MOH) – Dengue guidelines)
^
23,
24
^; (iii) have plasma ferritin levels > 2000 ng/mL ; (iv) agree to come back for two follow up visits between day 30 – 35 and at around day 90 afterillness onset; and (v) provide written informed consent.

Exclusion criteria include: (i) pregnancy (confirmed by either clinical examination or urine dipstick for human chorionic gonadotropin hormone); (ii) localizing features suggestive of an alternative diagnosis; (iii) taking immunosuppressive drugs or other biologics in the last month; (iv) underlying malignancy or immunosuppression; (v) children less than 12 years of age; (vi) have baseline GFR < 30 ml/min; (vii) having a neutrophil count < 1.0 × 10
^9^/L; (viii) being treated for tuberculosis; (ix) HBsAg-positive; (x) taking any drug with significant interaction with anakinra (concomitant medication and drug interactions); (xi) patients who are considered unlikely to attend follow-up visits because of long travelling distance to the study clinic or other reasons.

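### The only planning SD for delta mSOFA comes from adults with severe dengue, so the single power claim is not shown to hold for the wider population the trial enrols

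*Protocol article*

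**What the plan says.** The sample-size paragraph takes delta mSOFA as approximately normal "with a standard deviation of 2.4", "which was based on a cohort of 38 adults admitted with severe dengue". From this it derives 80 patients per group "to detect a between-group difference of at least 1.0 point" "with 80% power and 5% type-I error rate". The SD is attributed to that cohort. The 1.0-point difference is attributed to nothing.

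The eligibility criteria describe a wider group. Patients must be at least 12 years old, must "have a clinical diagnosis of dengue and at least one warning sign or severe dengue", and must have ferritin above 2000 ng/ml. The Design section says they come from intensive care, the Emergency Department and the general dengue wards, and that ward is the stratification factor. The article gives no expected share of severe cases and no quota.

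**The concern.** A sample-size calculation describes the population that supplied its inputs. Here the one variability figure comes from adults who already had severe dengue, with no mention of selection on ferritin. The trial population differs in three ways: less severe disease is admitted, adolescents are admitted, and everyone is selected on ferritin. Each could change the spread of delta mSOFA. Case mix could also change the mean difference that the drug can produce.

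This is not a detail left to a later document. The paragraph makes a finished power claim from a named source, and that source does not match the stated eligibility. If the claim is wrong for the enrolled mix, the trial could be clearly better or clearly worse powered than readers are told, and a null result would be hard to interpret.

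**Working it through.** **Inputs from the article.** SD 2.4; difference 1.0; 80 per group; 1:1 allocation; 5% type I error; 80% power. Sidedness is not stated in the sample-size sentence. Two-sided is taken here because the primary comparison is to be reported with a 95% confidence interval. The formulas are for a two-sample comparison of means (normal approximation), whereas the planned analysis is a mixed-model slope comparison, for which the article gives no planning inputs.

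**Step 1: the plan's own figure.** n per group = 2 × (1.960 + 0.842)² × 2.4² / 1.0² = 2 × 7.85 × 5.76 = 90.4, so 91 rather than 80. At 80 per group the standard error is 2.4 × √(2/80) = 0.379, and power = Φ(1.0/0.379 − 1.960) = Φ(0.675) = 75%. With one-sided 5% the result is 72 per group, with 84% power at 80. Neither choice reproduces 80. This shortfall is separate from the population question, but it shows where the claim stands even for a purely severe population.

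**Step 2: precision of the SD in its own population.** With 38 patients, the 95% confidence interval for an SD of 2.4 is 1.96 to 3.10. Over that interval, power for 1.0 point at 80 per group runs from 90% down to 53%.

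**Step 3: detectable difference over a range of SDs.** At 80% power, two-sided 5% and 80 per group, the detectable difference is 2.802 × SD × √(2/80) = 0.443 × SD. The SDs of 1.2 and 1.6 are assumptions for a milder mix.

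| SD | Detectable difference |
|---|---|
| 1.2 | 0.53 |
| 1.6 | 0.71 |
| 2.4 | 1.06 |

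**Step 4: why the direction is open.** Power at 80 per group is shown for assumed pairs of SD and true mean difference. SD 3.0 lies near the upper limit from Step 2.

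| SD | 0.6 points | 0.8 points | 1.0 point |
|---|---|---|---|
| 1.2 | 89% | 99% | about 100% |
| 1.8 | 56% | 80% | 94% |
| 2.4 | 35% | 56% | 75% |
| 3.0 | 24% | 39% | 56% |

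If a milder mix lowers the SD to 1.8 and leaves the effect at 1.0, power rises to 94%. If the effect also falls to 0.6, power is 56%. The article supplies neither figure for warning-sign patients.

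**Step 5: what the article says about case mix.** In Cytokine storm and inflammatory biomarkers, "63% with severe disease and 33% with moderate disease had ferritin levels > 2000 ng/ml". The severe share of the ferritin-eligible pool is 0.63s / (0.63s + 0.33m), where s and m are the shares of severe and moderate patients among those screened. Background says that "approximately 5–10% of hospitalized patients will develop severe manifestations". If everyone else counts as moderate, the non-severe share of the eligible pool is 0.95 × 0.33 / (0.95 × 0.33 + 0.05 × 0.63) = 91% at s = 5%, and 83% at s = 10%. With 10% severe and 10% moderate it is 34%; with 10% and 20% it is 51%. Non-severe patients are the majority only while severe cases stay below 0.33 / (0.33 + 0.63) = 34.4% of the severe-plus-moderate pool. The article does not fix m, so it does not fix the mix.

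**The case against.** The strongest reply is that the mismatch may do no harm, or may even help. Milder patients may vary less, and at a fixed 1.0-point effect a smaller SD raises power. This is correct, and it is why no loss of power can be asserted.

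Two stronger readings are tempting, and the article supports neither.

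- **That warning-sign patients will form most of the sample.** This needs three assumptions: that moderate disease in the ferritin cohort means warning signs, that the 5–10% background figure is the case mix at screening, and that nearly all other inpatients are moderate. The background figure concerns patients who go on to develop severe manifestations, and one of the two recruitment strata is intensive care with the Emergency Department. A mix with fewer warning-sign than severe patients is possible.
- **That patients without organ failure cannot move on the score.** The endpoint is change over 4 days, and a patient who starts low can worsen on placebo. Preventing progression is part of the stated rationale. The mSOFA components are in an appendix that is not shown, so baseline values near the floor cannot be checked.

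It can also be said that sensitivity of power to the SD often sits in a full protocol or analysis plan. That is fair for extra scenarios. It does not excuse a single power figure stated as achieved from a source population narrower than the trial's.

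**Conclusion.** The point holds in a limited form. The SD of 2.4 is documented only for 38 adults with severe dengue, the 1.0-point difference has no stated source, and the article does not justify either for a population that includes warning-sign patients and adolescents and is selected on ferritin. The claim of 80% power for 1.0 point at 80 per group is therefore not shown to hold for the patients enrolled. That is less than showing it to be false for them.

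The detectable difference roughly doubles across the range considered, from 0.53 at SD 1.2 to 1.06 at SD 2.4. Even if 2.4 is accepted, power for 1.0 point is about 75% rather than 80%. These figures assume a two-sided 5% test of two means with complete data; the lower SDs are assumed. Whether true power is above or below the stated value cannot be settled from the article, because the SD, the effect and the share of warning-sign patients are all missing.

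**What to change.** 1. In the sample-size paragraph, state that SD 2.4 is from adults with severe dengue and give the basis for the 1.0-point difference. Replace the single power claim with the difference detectable at 80% power (two-sided 5%, 80 per group) over a range of SDs: about 0.53 for SD 1.2, 0.71 for SD 1.6 and 1.06 for SD 2.4, noting that power for 1.0 point at SD 2.4 is about 75%.
2. At one of the data monitoring committee reviews already scheduled after every 50 recruits, compute the pooled SD of delta mSOFA blind to arm and the share with severe dengue at randomisation, then restate the detectable difference. The pooled figure slightly overstates the within-arm SD: with a true difference of 1.0 and SD 2.4 it would be √(2.4² + 1.0²/4) = 2.45.

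The cost is one reworded paragraph and one blinded calculation, with no extra patients or procedures. Those reviews are described as being for safety and tolerability, so the calculation has to be added to their remit. Recruitment has begun, and the article requires approval for amendments to approved documents where necessary. The downside is that the stated power becomes less favourable at SD 2.4. Adding WHO severity as a second minimisation factor is a separate design choice, and this point does not depend on it.

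### The stated 80% power does not follow from the stated inputs: read as two-sided 5%, 80 patients per group give about 75% power for a 1.0-point difference in delta mSOFA

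*Protocol article*

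**What the plan says.** The Protocol article, Statistical considerations, Sample size, treats delta mSOFA as approximately normal "with a standard deviation of 2.4, which was based on a cohort of 38 adults admitted with severe dengue". From this it derives a "sample size of 80 patients per group to detect a between-group difference of at least 1.0 point with 80% power", with a "5% type-I error rate". The paragraph gives no sidedness, no allowance for loss, no baseline correlation and no gain from repeated measurements.

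The Design section sets equal allocation ("Participants will be randomized 1:1 (anakinra:placebo") and a total of 160, which is 2 × 80. The Statistical analysis paragraph plans a linear mixed-effects model for mSOFA over the first 4 days. The treatment effect is the difference in slope, to be "presented with a corresponding 95% confidence interval".

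**The concern.** The paragraph reads as a complete two-sample calculation for a difference in means: an SD, a target difference, a power, an error rate and a resulting group size. When these are put into the usual formula, the group size does not come out.

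This sentence is the article's only justification for the trial's size on its primary endpoint. If the power is about 75%, the chance of missing a true 1.0-point effect is about 25%, against the 20% that the text implies. Anyone who weighs a null result against the planned power would then use a figure that the listed inputs do not deliver.

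**Working it through.** **Inputs.** From the Sample size paragraph: SD σ = 2.4, difference δ = 1.0, power 80%, type-I error 5%, n = 80 per group. From Design: allocation 1:1. Assumed, because the text does not say: a two-sided test. One-sided is tried as well.

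**1. Attempt to reproduce 80, two-sided.**

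n per group = 2(z₀.₉₇₅ + z₀.₈₀)²σ²/δ² = 2 × (1.960 + 0.8416)² × 2.4²/1.0² = 2 × 7.849 × 5.76 = 90.4, so 91.

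The t-test calculation gives 91.4, so 92. The stated 80 is 11 to 12 per group below this, or 22 to 24 in total.

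**2. Power at 80 per group, two-sided.**

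- SE = 2.4 × √(2/80) = 0.3795, and δ/SE = 1.0/0.3795 = 2.635.
- Power = Φ(2.635 − 1.960) = Φ(0.675) = 75.0%.
- The noncentral t gives 74.5%.

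**3. Difference detectable with 80% power at 80 per group.**

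0.3795 × (1.960 + 0.8416) = 1.06 by the normal approximation. The t-test gives 1.07.

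**4. Could a one-sided test explain 80?**

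n = 2 × (1.645 + 0.8416)² × 5.76 = 71.2, so 72. The t-test gives 71.9, also 72. At 80 per group the one-sided power is 83.9% (normal) or 83.6% (t-test). Neither the size nor the power matches.

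**5. Could rounding of the SD explain it?**

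The smallest SD that rounds to 2.4 is 2.35. It needs 86.7, so 87 per group (normal), or 87.7, so 88 (t-test). An n of 80 needs an SD of about 2.26 (normal) or 2.24 (t-test), and neither rounds to 2.4.

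**6. Could a rank test explain it?**

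Dividing by the Wilcoxon efficiency of 0.955 gives 91/0.955 = 95.3, so 96 two-sided, and 72/0.955 = 75.4, so 76 one-sided. Neither is 80.

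**7. What does give 80?**

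- One-sided 5% with 10% loss: 72/0.9 = 80.
- Two-sided 5% with a smaller residual variance: 1 − 80/90.4 = 11.5% (normal) or 1 − 80/91.4 = 12.5% (t-test), so a reduction of about 12%. If this came from baseline adjustment, the correlation would be √0.115, about 0.34.

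The document states neither of these.

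**The case against.** The strongest reply is that the two-sided test is my inference. The text says only "5% type-I error rate", and one-sided testing with a 10% loss allowance reproduces 80 exactly. That may well be where the number came from. What stands is that sidedness is not a stated input, and that the full protocol may hold an assumption that explains 80. What does not stand is the sentence as printed: it presents 80 as the consequence of the inputs it lists, and one-sided 5% on those inputs gives 72. The planned 95% interval also points to a two-sided reading.

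A second reply is that the primary analysis is a mixed model on daily scores, which may be more efficient than a comparison of change scores. That is fair, and it may recover some or all of the shortfall. The paragraph, however, uses only the SD of the change score and claims no gain. It fixes neither the number of scores nor the variance components, so the gain cannot be worked out from the document.

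A reader might also infer that the plan makes no allowance for missing scores or withdrawals. The document does not support that as a criticism. The 80 could already contain such an allowance, a condensed article may leave it to the full protocol, and the mixed model uses partial daily data.

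Finally, the gap is modest. No estimate, test or analysis rule changes, and a null result can be read from its confidence interval.

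**Conclusion.** The point holds as an error in the stated power for the primary endpoint. With SD 2.4, a 1.0-point difference and 5% read as two-sided, 80 per group give 74.5% to 75.0% power, about 5 percentage points below the claim. The conclusion assumes a two-sided test and a plain comparison of mean change, which is what the paragraph describes. The mismatch itself does not depend on the first assumption, because the one-sided reading misses 80 as well.

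A reader might go further and conclude that the trial is too small and must enrol more patients. The documents do not support that. The detectable difference moves only from 1.0 to about 1.07 points, and the planned model could have more power than this calculation shows. The defect lies in what is claimed for 160 patients, not in the number 160.

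**What to change.** Make one of two changes in the Sample size paragraph.

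- **Restate the power:** 80 per group gives about 75% power to detect 1.0 point, or 80% power to detect about 1.07 points (SD 2.4, two-sided 5%).
- **Keep 80% for 1.0 point:** state the sidedness and the assumption that yields 80. That could be a loss allowance, or a variance reduction of about 12% with the correlation or model gain behind it.

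If 80% is kept on the basis of a one-sided 5% test, the paragraph should also say how that fits with the 95% interval in the analysis section.

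The cost is a sentence. No patients, visits or analyses are added. If the power is restated, it becomes slightly less favourable. The article reports the trial as ongoing, so the text can be corrected before results are read.
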